## Abstract

**Background:**

Workplace cyberbullying harms the psychological and social functioning of professionals working in an organization and may decrease the productivity and efficiency of daily life tasks. A recent study on trainee doctors across 8 different United Kingdom National Health Service trusts found health issues and job dissatisfaction in people who have experienced workplace cyberbullying. This disabling effect is even more noticeable in low-socioeconomic communities within low-income countries. In Malaysia, there is a need to create a personalized mobile mental health intervention program for health care professionals. These programs should be directed to prevent and decrease psychosocial issues and enhance coordination among health care professionals to solve health issues in the community.

**Objective:**

Our main objective is to study the pre-effects and posteffects of the Personalized Mobile Mental Health Intervention (PMMH-I) for workplace cyberbullying in public and private hospitals in Malaysia.

**Methods:**

A hospital-based multimethod multi-analytic evidential approach is proposed, involving social and psychological health informatics. The project has been subdivided into 3 stages, starting with Phase 1, a prevalence study, followed by exploratory studies. Phase 2 consists of a quasi-experimental design, whereas the development of a prototype and their testing will be proposed in Phase 3. Each stage includes the use of quantitative and qualitative methods (mixed-method program), using SPSS (version 26.0; IBM Corp) and Stata (version 16.1; StataCorp) as tools for quantitative research, and NVivo (version 1.0; QSR International) and Atlas.ti (version 9.0.16; ATLAS.ti Scientific Software Development GmbH) for qualitative research.

**Results:**

The results of this study will determine the pre- and posteffectiveness of an integrated PMMH-I for health care professionals. The prototype system platform will be developed and implemented in a public and private hospital. Results from Phase 1 will be published in 2021, followed by the implementation of Phase 2 in subsequent years.

**Conclusions:**

This study will provide evidence and guidance regarding the implementation of a personalized mobile mental health intervention for health care professionals into routine public and private hospitals to enhance communication and resolve conflicts.

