## Introduction

### Background

Suicidal behavior, depression, loneliness, anxiety, and somatic symptoms are among the most common effects of cyberbullying experienced by students [1] and adolescents [2]. There is a huge psychological impact (ie, depression) on people who experience workplace bullying from coworkers, such as nurses [3-6], health care providers, and employers [7], especially among women. The prevalence of cyberbullying among first-year trainee doctors who reported experiencing it at least 1 time was 46.2% [8]. Another study found a high prevalence rate (28%) of cyberbullying among a diverse workforce sample in the United States [9].

Malaysia has a high mobile penetration rate due to thriving e-commerce [10]. The problematic use of smartphones can lead to addiction; increased use of mobile phones in India has led to an increase in technology addiction [11,12]. This addiction leads to depression, anxiety, stress, and self-esteem issues [13]. A school-based study identified a strong correlation between pathological internet use and cyberbullying in Greece [14]. However, there is a lack of evidence that pathological mobile use could lead to an increase in cyberbullying in the workplace. Most published studies, systematic reviews, and interventions are limited to cyberbullying at school, colleges, universities, or the young population.

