### Research Questions

We aim to explore the following 4 research questions in this study: (1) What is the current workplace cyberbullying status among Traditional Chinese Medicine practitioners (TCM) in Malaysia? (2) What is the pre- and postefficacy of the Personalized Mobile Mental Health Intervention (PMMH-I) on the prevalence of measurable factors (ie, depression, anxiety, and stress) in workforce cyberbullying on TCM practitioners? (3) What are the moderating and mediating factors of workplace cyberbullying on TCM practitioners? (4) What is the technological feasibility of implementing the integrated PMMH-I as a component of routine hospital-based systems?

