### Main Intention and Objective

This study's main intention is to give awareness and authority to the community of health care professionals against cyberbullying by developing a Personalized Mobile Mental Health Intervention program (PMMH-I) in partnership with all health care providers. This partnership will seek to form alliances with public and private institutions to ensure the success and continuation of the program. The PMMH-I program will aim to reduce the psychometric properties of cyberbullying through awareness and adaptation of technology.

The main objective of this protocol is to develop and implement the PMMH-I program to decrease the psychometric properties of cyberbullying in the hospital-based setting in Malaysia. We hypothesize that the creation of PMMH-I programs will come about by executing a PMMH-I strategy that permits the fusion of global and local knowledge. PMMH-I promotes health care community development, thereby increasing social integration between different health care providers such as doctors, nurses, traditional and complementary medical practitioners, pharmacists, and other health care providers.

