#### Prevalence Study

The specific objectives of this study include (1) evaluating the overall prevalence rate of workplace cyberbullying and its related psychological impacts (depression, anxiety, and stress) on TCM practitioner; (2) understanding the measures associated with various forms of workplace cyberbullying on age, gender, and frequency; and (3) understanding the measure associated with workplace cyberbullying on perpetrators responsible for workplace cyberbullying. The current research will be a survey-based online cross-sectional prevalence study. TCM practitioners are considered a hard-to-reach population; thus, we will conduct a nonprobability snowball sample of 1023 adults (3% precision, 95% confidence level) according to the number of TCM practitioners, which was approximately 15,000 in 2011 [16]. The Hamilton Depression Scale (HAM-D) [17], the Hamilton Anxiety Scale (HAM-A) [18], and the clinical anger scale [19] will be used to assess the psychological impact on TCM practitioners. The Cyberbullying Questionnaire (CBQ) and a short version of a cyberbullying behavior questionnaire (CBQ-S), adapted from Jönsson et al [20], will be used to identify the prevalence among TCM practitioners; these selected questionnaires were already validated in Sweden and the US adult population [20]. The prevalence will also investigate the association with moderating variables (age and gender). Perpetrators of cyberbullying will also be assessed in the specific identification of the prevalence of workplace cyberbullying using the CBQ and CBQ-S questionnaires. The sampling method to understand perpetrator effects in the prevalence will similarly be addressed. The survey will also include a socioeconomic assessment, including education, income, home characteristics, and commodities. The survey will be conducted online due to the current pandemic situation caused by COVID-19, following the CHERRIES guidelines given by Gunther Eysenbach [21].

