#### Quasi-experiment with Nonequivalent Pretest–Post-test Control Group Design

The study design for this stage is quasi-experimental, in which the groups are nonrandomized into intervention and control groups and selected purposively. This study will be conducted in public hospitals and private hospitals located in Malaysia. All hospitals are eligible to participate. The selection of hospitals will be randomized for the implementation of the interventions. The randomization of hospitals will be performed by online statistical computing web programming to generate the randomization schedule [22]. The current methodology will help reduce selection bias in the study.

This intervention study will be conducted on TCM practitioners specifically. A baseline assessment will be done, in the intervention and control hospital, to measure the burden of bullying and its correlates using the CBQ and CBQ-S. This stage will begin after the investigation of prevalence and exploratory research. First, baseline information will be collected within 3 months, and then the intervention will be monitored twice after a regular period of 6 months in order to monitor the consistency of the intervention program.

The intervention program will be designed and finalized after (1) a systematic review of systematic reviews of previously published literature on bullying and the effectiveness of antibullying intervention programs; (2) the conducting of focus group discussions with TCM practitioners, patients, and other health care providers (to explore the perceptions, beliefs, and suggestions regarding bullying prevention programs); and (3) the conducting of a consultation workshop with all the stakeholders. The bullying intervention program (BIP) will pretest among 50 participants, which will include health care providers, TCM practitioners, and patients. The multicomponent hospital-based intervention strategy will be administered at 3 levels: (1) patients, (2) TCM practitioners, and (3) other health care providers. All the data of participants in this study will be password-protected and safe using Microsoft OneDrive. The recruitment of participants will follow the same procedure described for the exploratory study and prevalence study.

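### Effectiveness results and implementation guidance are promised for health care professionals, but effectiveness outcomes are described only for TCM practitioners

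*Protocol article*

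**What the plan says.** **What is promised.** Abstract, Results: "The results of this study will determine the pre- and posteffectiveness of an integrated PMMH-I for health care professionals". Abstract, Conclusions, adds "evidence and guidance regarding the implementation of a personalized mobile mental health intervention for health care professionals into routine public and private hospitals". In the body, Main Intention and Objective says that the programme is for the community of health care professionals and is meant to increase integration between "different health care providers such as doctors, nurses, traditional and complementary medical practitioners, pharmacists, and other health care providers".

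**What is studied.**
- Research Questions: the questions on current status, on efficacy, and on moderators and mediators each name TCM practitioners. The fourth, on technological feasibility, names no profession.
- Prevalence Study: a "nonprobability snowball sample of 1023 adults (3% precision, 95% confidence level) according to the number of TCM practitioners, which was approximately 15,000 in 2011".
- Exploratory Study: a sample of 384, with the emotion reaction model applied to TCM practitioners.
- Quasi-experiment (Phase 2): "This intervention study will be conducted on TCM practitioners specifically". The cyberbullying questionnaires (CBQ and CBQ-S) are given at baseline in intervention and control hospitals.
- Phase 3, Data Collection and Analysis: only those who completed Phase 2 continue.

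**The concern.** The population in the promised results and conclusion is wider than the population in which effectiveness is measured. If the plan is carried out exactly as written, it ends with a statement that the intervention works, or does not, for health care professionals in general, based on data from one occupation.

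Hospitals deciding whether to offer the programme to doctors, nurses or pharmacists are the natural readers of the Abstract. They would take it as evidence for staff in whom no effect is estimated. The article offers no argument for carrying the effect over from TCM practitioners to the other professions.

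**Working it through.** The point depends on no figure, so the check is a comparison of sections. The stated sample sizes serve only to confirm which population was sized.

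**Step 1: the sample sizes.** Formula: n0 = z² p(1 − p)/e², with z = 1.96 and p = 0.5 (p is an assumption; the article does not state it).
- Prevalence Study, e = 0.03: n0 = 3.8416 × 0.25 / 0.0009 = 1067.1. With a finite population correction for N = 15,000, n = 1067.1 / (1 + 1066.1/15,000) = 996.3. The stated 1023 is (1023 − 996.3)/1023 = 2.6% higher. This is close, though not exact, and fits sizing on the TCM practitioner count, as the text says.
- Exploratory Study, e = 0.05: n0 = 3.8416 × 0.25 / 0.0025 = 384.16, which matches 384. This figure uses no population size; the section itself names TCM practitioners as the subject.
- No sample size is stated for doctors, nurses, pharmacists or other providers.

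**Step 2: population by component.**

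| Component | Population for outcomes |
|---|---|
| Abstract, Results and Conclusions | health care professionals |
| Main Intention and Objective | doctors, nurses, traditional and complementary practitioners, pharmacists, others |
| Research questions 1 to 3 | TCM practitioners |
| Research question 4 (feasibility) | none named |
| Prevalence Study | TCM practitioners |
| Exploratory Study | TCM practitioners |
| Phase 2 quasi-experiment | TCM practitioners |
| Phase 3 post-test | Phase 2 completers, hence TCM practitioners |

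**Step 3: where other providers appear, and whether that yields effectiveness data.**
- Focus groups and the stakeholder workshop (Phase 2): these shape the programme before it is tested.
- Pretest in 50 mixed participants (Phase 2): a development step with no described comparison between groups.
- One of three levels at which the intervention is administered (Phase 2): delivery to a group is not measurement in that group. The baseline questionnaires are described in the paragraph that limits the study to TCM practitioners.
- An expert from each stakeholder group in interface design and prototype testing (Phase 3): design and usability input.
- Performance and satisfaction questionnaires (Phase 3): respondents are not stated, so some feasibility input from other professions is possible.

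None of these gives a pre-post or between-group effect for a profession other than TCM practitioners.

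**The case against.** The strongest reply is that this is loose summary wording and not a fault in the design. The body says repeatedly and openly that TCM practitioners are studied, and they are themselves one kind of health care provider. The Conclusions sentence is about implementation, which is closest to the fourth research question, and that question names no profession. Other providers do take part, and they may answer the Phase 3 questionnaires.

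Much of this stands. A reader of the Methods would not be misled about who is enrolled, and it would be wrong to say that other professions contribute nothing at all. But the Results sentence of the Abstract concerns effectiveness, not feasibility, and the body repeats the broad aim when it lists the professions. One occupation on that list cannot establish effectiveness for the rest.

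Four stronger inferences are tempting but not supported:
- *That every research question is confined to TCM practitioners.* Only three of the four are.
- *That the trial cannot answer its own question.* Its population-specific questions are about TCM practitioners, and the enrolled population matches them.
- *That the 28% and 46.2% prevalences in Background measure how far professions differ.* They come from different studies, in a diverse US workforce sample and in first-year trainee doctors. No definition is given for the 28%, and neither sample is of TCM practitioners. The gap cannot be attributed to profession and says nothing about whether an intervention effect carries over.
- *That the survey records no workplace type.* The Prevalence Study lists only what its socioeconomic part includes. That list in a condensed article does not show what the full questionnaire lacks.

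**Conclusion.** The point holds as a mismatch between the claimed and the studied population. Effectiveness is promised for health care professionals, while every effectiveness outcome that the article describes is in TCM practitioners. Of the four occupational groups named in Main Intention and Objective, three (doctors, nurses and pharmacists), together with the residual category of other providers, have no effectiveness sample. No numerical bias can be attached to this, and none is claimed.

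The conclusion rests on three readings:
- TCM practitioners fall within the traditional and complementary group.
- The Phase 2 restriction to TCM practitioners governs the baseline and follow-up questionnaires, although the intervention is delivered at three levels.
- Limiting Phase 3 to Phase 2 completers carries that restriction forward.

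The design can support a conclusion about TCM practitioners. It cannot support the general one as worded.

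**What to change.** - **Abstract, Results and Conclusions:** limit the effectiveness results and the conclusion drawn from them to TCM practitioners in the participating hospitals.
- **Main Intention and Objective:** align the aim with the same population. The list of other professions can stay as the community that the programme hopes to serve later, provided that it is not presented as the population in which effectiveness is tested.
- **Input from other professions** (focus groups, workshop, pretest, design and prototype testing, any satisfaction questionnaires): describe and report it as development or feasibility information only.

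The cost is a change of wording in three places and a narrower claim. No change to sample, instruments or schedule is needed. Keeping the broad claim would instead require outcome samples from the other professions, which is a much larger undertaking.

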**International Registered Report Identifier (IRRID):**

PRR1-10.2196/23112

## Introduction

### Background

Suicidal behavior, depression, loneliness, anxiety, and somatic symptoms are among the most common effects of cyberbullying experienced by students [1] and adolescents [2]. There is a huge psychological impact (ie, depression) on people who experience workplace bullying from coworkers, such as nurses [3-6], health care providers, and employers [7], especially among women. The prevalence of cyberbullying among first-year trainee doctors who reported experiencing it at least 1 time was 46.2% [8]. Another study found a high prevalence rate (28%) of cyberbullying among a diverse workforce sample in the United States [9].

Malaysia has a high mobile penetration rate due to thriving e-commerce [10]. The problematic use of smartphones can lead to addiction; increased use of mobile phones in India has led to an increase in technology addiction [11,12]. This addiction leads to depression, anxiety, stress, and self-esteem issues [13]. A school-based study identified a strong correlation between pathological internet use and cyberbullying in Greece [14]. However, there is a lack of evidence that pathological mobile use could lead to an increase in cyberbullying in the workplace. Most published studies, systematic reviews, and interventions are limited to cyberbullying at school, colleges, universities, or the young population.

### Research Questions

We aim to explore the following 4 research questions in this study: (1) What is the current workplace cyberbullying status among Traditional Chinese Medicine practitioners (TCM) in Malaysia? (2) What is the pre- and postefficacy of the Personalized Mobile Mental Health Intervention (PMMH-I) on the prevalence of measurable factors (ie, depression, anxiety, and stress) in workforce cyberbullying on TCM practitioners? (3) What are the moderating and mediating factors of workplace cyberbullying on TCM practitioners? (4) What is the technological feasibility of implementing the integrated PMMH-I as a component of routine hospital-based systems?

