### Phase 3: Electronic Anticyberbullying Monitoring System

#### Interface Design

An expert from each stakeholder group (TCM practitioners, other health care professionals, patients, and IT experts) will be involved in the interface design, information system design, and prototype testing. The system’s overall performance and satisfaction will be acquired through questionnaires (questionnaires are available upon request). The CBQ and CBQ-S will be used to determine the effectiveness of an intervention program using a prototype (post-test). The compilation of this research will be used to design the Personalized Mobile Mental Health Intervention (PMMH-I). The duration for stage 3 will be 6 months.

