#### Data Collection and Analysis

The recruitment of participants will follow the same procedure as was described for the exploratory study and prevalence study. The participant will be invited to join through a webinar to complete the questionnaire. Only the participants who completed Phase 2 will be asked to continue. The prototype will be given to them, and a brief training will be provided through a 30-minute webinar. Stage 3 participants will be limited to the Stage 2 completers in order to gauge the effectiveness of the Step 2 intervention program and whether the prototype is capable of reporting cyberbullying effectively. Thematic analysis will be done on the data yielded from the control and intervention groups. All the data of participants in this study will be password-protected and safe using Microsoft OneDrive.

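### No stated Phase 3 measure addresses operation within hospital systems, which research question 4 asks about, and both the completers-only rule and the design experts' role in testing are likely to favour the prototype

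*Protocol article*

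**What the plan says.** The Research Questions section of the protocol article sets the fourth question: "What is the technological feasibility of implementing the integrated PMMH-I as a component of routine hospital-based systems". The abstract's Results paragraph adds: "The prototype system platform will be developed and implemented in a public and private hospital". The abstract's Conclusions paragraph expects the study to guide adoption in routine public and private hospital practice.

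Phase 3 is the stage that tests the prototype. Under Interface Design, the plan names one expert per stakeholder group: TCM practitioners, patients, IT experts and other health care professionals. Those named "will be involved in the interface design, information system design, and prototype testing". On the system itself, the text says that "overall performance and satisfaction will be acquired through questionnaires"; the forms can be had on request. The CBQ and CBQ-S serve as the effectiveness post-test.

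Under Data Collection and Analysis, "Only the participants who completed Phase 2 will be asked to continue". Then: "The prototype will be given to them, and a brief training will be provided through a 30-minute webinar". The reasons given for the restriction are to gauge the effectiveness of the preceding programme and "whether the prototype is capable of reporting cyberbullying effectively". A thematic analysis covers data from the control and intervention groups. The Results section of the article allows 6 months for development, implementation, pilot testing and post-testing, subject to funding.

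**The concern.** The question is about a tool working as part of a hospital's routine systems. The measures describe how individual users judge the prototype, how they score on cyberbullying scales, and what themes emerge. A favourable result on all of them would leave the question open, because none is stated to observe the prototype operating within a hospital system.

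Two choices also affect whose judgement is recorded. People who left Phase 2 are not asked, so any for whom the programme was unworkable are absent from the result. The experts who shaped the system are among those who test it, and they are not independent of it. Both choices probably push towards a good rating. At stake is the study's closing claim about routine hospital use, which could rest on ratings from a selected group on measures that do not address hospital operation.

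**Working it through.** The article gives no figure for this question: no Phase 2 or Phase 3 enrolment, no completion rate and no feasibility threshold. There is nothing to reproduce, so the check is a comparison of the text followed by a short piece of algebra.

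**Step 1. Stated measures against the question.**

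| Phase 3 measure | Where stated | What it addresses | Tied to operation in hospital systems? |
|---|---|---|---|
| Performance and satisfaction questionnaires | Interface Design | The system as respondents judge it | Not stated; content not shown |
| CBQ and CBQ-S post-test | Interface Design | Effectiveness of the programme | No |
| Thematic analysis | Data Collection and Analysis | Data from control and intervention groups | Not stated |

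The stated purposes of the Phase 3 restriction are programme effectiveness and reporting capability. Hospital operation is not among them.

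**Step 2. Who supplies the evidence.** Two groups handle the prototype: the stakeholder experts, who also take part in design, and the Phase 2 completers. Non-completers supply nothing.

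**Step 3. What the completers-only rule can do to a rating.** Suppose the questionnaire result is reduced to the share of people giving a favourable rating, and every completer answers. Let c be the share of Phase 2 enrollees who complete, s the favourable share among completers, and q the share that would be favourable among non-completers if asked.

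- Completers-only result: s
- Result for all enrolled: c·s + (1 − c)·q
- Difference: s − [c·s + (1 − c)·q] = (1 − c)(s − q)

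The documents give none of c, s or q. The values below are assumptions, chosen only to show how far the answer depends on them. With s = 0.80, the difference is:

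| c | q = 0 | q = 0.40 | q = 0.80 |
|---|---|---|---|
| 0.9 | 0.1 × 0.80 = 0.08 | 0.1 × 0.40 = 0.04 | 0 |
| 0.7 | 0.3 × 0.80 = 0.24 | 0.3 × 0.40 = 0.12 | 0 |
| 0.5 | 0.5 × 0.80 = 0.40 | 0.5 × 0.40 = 0.20 | 0 |

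The difference runs from 0 to 40 percentage points on assumed inputs alone. It is zero whenever non-completers would rate the prototype as completers do. The column q = 0 is an extreme case. The plan as written collects nothing from non-completers that would show which column applies.

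The effect of the design experts cannot be put into figures. The article does not say whether they complete the questionnaires.

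**The case against.** The other side has several good points, and they limit what can be said.

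- **Measures.** The questionnaires cover performance as well as satisfaction, and their items are not shown. Some could concern technical integration, so it would be wrong to say that the answer will be a satisfaction score alone.
- **Delivery.** A reader might infer that the prototype is handed over by webinar and so sits outside the hospital. The text says only that training is given that way.
- **Hospital setting.** A reader might infer that integration is untested. The abstract plans implementation in a public and private hospital, the Results section plans pilot and post-testing, and a condensed article may leave integration criteria to the full protocol. What can be said is that no stated Phase 3 measure is linked to that implementation.
- **Testers.** The experts are not the only testers, because completers also use the prototype. Stakeholder involvement in both design and testing is not an error in itself.
- **Direction of bias.** A reader might infer that feasibility is overstated. Phase 2 has a control group, so completing it is not the same as adhering to the intervention. The prototype is described as reaching participants in Phase 3, so those who left Phase 2 had not rejected it. Upward bias is plausible but not shown.
- **Scope.** The question concerns technological feasibility. The share of a hospital's practitioners who would take up the tool is a different question and should not be read into it.

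Two things survive. The completers-only rule and the experts' double role are choices made in the text, not details left for later. And the measures that the article does name are not tied to what the question asks.

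**Conclusion.** The point holds in a limited form. Followed as written, Phase 3 can describe the performance, acceptability and reporting capability of the prototype among people who finished Phase 2. It cannot by itself support a conclusion about technological feasibility within routine hospital systems.

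Selection of completers and testing by design experts are both likely to favour the prototype. The size of that effect cannot be derived from the documents and may be zero. This rests on reading the listed measures as the ones meant to answer the question, and on the unseen questionnaires having no items on hospital operation. If they do contain such items, the mismatch narrows, but the restriction to completers and the experts' double role remain.

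**What to change.** 1. **Denominator.** Report the Phase 3 performance and satisfaction results with the number enrolled in Phase 2 as the denominator, alongside the completers-only result. Offer the prototype and questionnaire to non-completers where possible. Where they cannot be reached, state that the all-enrolled share counts only favourable ratings actually obtained, and is therefore a lower bound (c·s in the notation above).
2. **Design experts.** Exclude any ratings by experts who took part in the design, or report them separately.
3. **Measure for research question 4.** Tie the question to a measure of the prototype's operation, for example its usage and reporting log, in the public and private hospital already foreseen in the abstract. Otherwise reword the question and its conclusion to performance and acceptability of the prototype among Phase 2 completers.

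When editing Data Collection and Analysis, also reconcile two statements: that recruitment follows the procedure of the prevalence and exploratory studies, and that only Phase 2 completers continue.

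The cost is slightly more analysis work, an invitation to non-completers, log extraction if that option is taken, and a feasibility statement that may be less favourable or narrower. Rewording alone costs almost nothing.
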